#### Primary Study End Point

##### Cognitive Performance (Neuropsychological Assessment Battery)

Cognitive functions will be assessed with tests previously used in HD patients (Costa et al., 2014; San et al., 2017; Zimmermann and Fimm, 2017b; Jafari et al., 2020), including Montreal Cognitive Assessment (MoCA), Trail Making Test A and B (TMTA and TMTB), Symbol Digit Modalities Test (SDMT), and computerized Test of Attentional Performance (TAP).

TAP score is selected as the main outcome of this study. The rationale for the selection of the main outcome is: (i) absence of significant level of test-related learning effect (Zimmermann and Fimm, 2017b), (ii) sensitive to effects of physical exercise (Noguera et al., 2019), and (iii) attention is one of the most affected cognitive domains in dialysis patients (Dixit et al., 2013). From the TAP test battery, we will include subtests Alertness, Selective attention, Divided attention, and Sustained attention. Low to moderate training effects were reported for the TAP subtests (Zimmermann and Fimm, 2017a). The authors stated that performance remained stable in most of the TAP tasks at most of the testing occasions, suggesting that the performance in these tasks is robust and unaffected by learning effects or task repetition harassment.

MoCA (Nasreddine et al., 2005) is a global cognitive function assessment tool covering eight cognitive domains. The psychomotor speed and executive function will be measured by TMTA and TMTB (Corrigan and Hinkeldey, 1987). The SDMT will be used to assess the psychomotor speed, efficiency of information processing, ability to switch between mental sets of the information and to maintain and manipulate information in working memory (Smith, 1982; Benedict et al., 2017). It is a reliable and valid test for assessing information processing speed, efficiency and executive functioning domains (Benedict et al., 2017).

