### Statistical Methods Including Sample Size Calculation

The primary outcome of this study will be the cognitive function assessed with the subtest “Alertness” of the Test for Attentional Performance (TAP, Version 2.3; Psytest, 2012).

The sample size was calculated using G*Power software (version 3.1; Faul et al., 2009) on the basis of the results of the study by Briken et al. (2014). For the calculation, the scores of the subtest alertness from the TAP test battery which were obtained from the group that completed bicycle ergometry before (376.91 ± 151.67) and after (302.64 ± 83.09) the treatment were used. The alpha error probability was set to 0.05, the 1-beta error probability to 0.80, while the effect size was taken from the previously mentioned research (0.314). A sample size of 22 participants was calculated. Allowing for a 20% attrition rate, a total number of 27 participants is required, with 14 participants assigned to each group. Analyses will be conducted according to the intention-to-treat principle.

SPSS 24.0 (SPSS, Inc., Chicago, IL, United States) software will be used for all calculations. All data will be presented with mean ± standard deviation and 95% confidence intervals when appropriate. Normality will be confirmed by using the Shapiro–Wilk test, with additional Q–Q plot visual inspection. Independent-sample *t* test, *χ*^2^, or Mann–Whitney tests will be used to determine group differences in clinical and demographic variables, depending on the comparison and test assumptions. The main effects will be analyzed using a mixed general linear model (GLM), taking into account the groups (EXP and CON) and time (baseline and after 12 weeks) as factors. After determining the interaction effect, a secondary analysis will be used to determine the time effect in both groups. Additionally, the degree of effect will be determined for dependent variables by using partial eta-squared (*η*^2^). Partial eta squared readings of 0.02, 0.13, and 0.33 were rated differences as small, moderate, and high (Pierce et al., 2004). Furthermore, in the case of unmatched baseline means, the analysis of covariance (ANCOVA) with baseline measurements entered as a covariate will be applied. For non-parametric data, a Friedman ANOVA will be applied, followed by a Sign-test separately for each scale. Statistical significance will be set at values of *p* < 0.05.

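### Baseline-adjusted ANCOVA should be the unconditional primary analysis, not a fallback used only when baseline means are judged unmatched

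*Protocol article*

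**What the plan says.** All of this is in the protocol article, Statistical Methods Including Sample Size Calculation, unless another section is named.

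- The primary outcome is the Alertness subtest of the Test of Attentional Performance.
- The main analysis is a mixed general linear model with group (EXP, CON) and time (baseline, 12 weeks) as factors.
- "After determining the interaction effect, a secondary analysis will be used to determine the time effect in both groups".
- Baseline adjustment is conditional: "in the case of unmatched baseline means, the analysis of covariance (ANCOVA) with baseline measurements entered as a covariate will be applied". The section does not say how a mismatch is judged, or whether ANCOVA then replaces the general linear model or sits beside it. The t, chi-squared and Mann–Whitney tests it lists are for clinical and demographic variables and are not tied to this rule.
- On sample size: "The alpha error probability was set to 0.05, the 1-beta error probability to 0.80", with an effect size of 0.314, 22 participants calculated, and 14 per group to be enrolled.

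**The concern.** Baseline Alertness is measured on every participant before randomisation, so adjusting for it costs almost nothing. The plan instead uses it as a covariate only after someone has looked at the baseline means and declared them different. Two things are at stake in a trial of 22 evaluable participants. The default analysis gives up precision that is available from data already collected. And which analysis carries the primary result is left to an undefined judgement on the observed data. The within-arm time tests are a lesser matter: they are not randomised comparisons and can be misread as evidence of a group difference.

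**Working it through.** **Inputs.** From the protocol: alpha 0.05, power 0.80, effect size 0.314, N = 22 evaluable, 14 per group enrolled, two groups 1:1, two time points, and pre/post values of 376.91 (SD 151.67) and 302.64 (SD 83.09) from one group of the cited exercise study. Assumed: 0.314 is Cohen's f; tests are two-sided; SDs are equal at the two visits; r is not stated and is taken as 0.3, 0.5 and 0.7.

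**1. Reproducing N = 22.** For a within–between interaction with m = 2 measurements, λ = f²·N·m/(1−r) with 1 and N−2 degrees of freedom. At r = 0.5 and N = 22, λ = 0.0986 × 22 × 2/0.5 = 8.68 and power is 0.800. Other values of r give N = 30 (r = 0.3), 20 (r = 0.6) and 16 (r = 0.7). So r = 0.5 matches the plan's figure.

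**2. The default is a change-score test.** With two visits the interaction contrast is (EXP follow-up − EXP baseline) − (CON follow-up − CON baseline), and its F statistic is the square of the t statistic on change. Setting λ equal to N·δ²/[4·2(1−r)] gives δ = 4f = 4 × 0.314 = 1.256 SD as the implied between-arm difference.

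**3. Precision.** In units of the outcome variance, the change score has variance 2(1−r) and ANCOVA has 1−r². The ratio is (1+r)/2.

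| r | Change | ANCOVA | Ratio | Total N for 80% power, change → ANCOVA (analytic) |
|---|---|---|---|---|
| 0.3 | 1.40 | 0.91 | 0.65 | 30 → 22 |
| 0.5 | 1.00 | 0.75 | 0.75 | 22 → 18 |
| 0.7 | 0.60 | 0.51 | 0.85 | 16 → 14 |

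**4. Power at 11 per arm and 1.256 SD (simulation).** Change score 0.66 / 0.80 / 0.95 and ANCOVA about 0.81 / 0.88 / 0.97 at r = 0.3 / 0.5 / 0.7. The analytic ANCOVA figure at r = 0.5 is 0.90; it ignores the small cost of estimating the adjustment.

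**5. What the conditional rule recovers at r = 0.5.** This depends on a trigger that the protocol does not give, so two are assumed.
- Baseline t-test p < 0.05: this needs a difference of 0.78 SD at 14 per arm (0.89 SD at 11). It fires in about 5% of trials, and power is 0.80, so almost nothing is recovered.
- Observed difference above 0.25 SD: it fires in about 56% of trials, and power is 0.85, so (0.85 − 0.80)/(0.88 − 0.80), a little over half, is recovered.

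**6. Chance imbalance.** Given a baseline difference D, the expected follow-up difference is δ + r·D. The change score subtracts all of D, so its error is −(1−r)·D. ANCOVA subtracts r·D and has no such error. For D = 0.5 SD and r = 0.5 the error is 0.25 SD. The pooled SD is √[(151.67² + 83.09²)/2] = 122.3, so this is about 31 ms. The chance of an imbalance of at least 0.5 SD is 2[1 − Φ(0.5/√(2/n))] = 19% at 14 per arm and 24% at 11. In simulated trials with baseline |t| above 1 but p > 0.05 (mean imbalance about 0.58 SD, r = 0.5), the change score was off by about 0.29 SD in the opposite direction. Its type I error in those trials was 0.077, against 0.051 for ANCOVA.

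**7. Overall type I error.** Fixed triggers (p < 0.05, 0.2 or 0.5, or a difference above 0.25 SD) gave 0.035–0.048 for r = 0.3–0.7. If whichever analysis is significant may be reported, the rate is about 0.08 at r = 0.3 and 0.07 at r = 0.5 and 0.7.

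**The case against.** The best defence is that the default is a valid and common analysis, unbiased over randomisation, and that a fixed switching rule is if anything slightly conservative. That stands. A condensed article may also leave the definition of a mismatch to a fuller document. That stands for the definition, but not for the conditional structure, which the article states.

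The size of the gain is also open to challenge. The 1.256 SD effect is about twice the pre–post change in the protocol's own figures, (376.91 − 302.64)/122.3 = 0.61 SD. At 0.61 SD, r = 0.5 and 11 per arm, power is about 27% for the change score and 33% for ANCOVA, so adjustment helps but does not make up for a smaller true effect. The largest gain needs r = 0.3, which does not reproduce N = 22. At r = 0.7 the gain is about 2 percentage points.

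Four stronger readings are tempting and are not supported.
- A reader might infer that chance imbalance goes uncorrected. The interaction subtracts the whole baseline difference; the fault is over-correction.
- A reader might infer that the trigger would almost never fire. That is true only under an assumed p < 0.05 rule, and the protocol names none.
- A reader might infer that the conditional rule inflates false positives. It does so only if the choice is discretionary.
- A reader might infer that the within-arm tests stand in for the randomised comparison, or that practice effects distort it. Those tests are expressly secondary and follow the interaction test. The outcome section does say "Low to moderate training effects were reported for the TAP subtests", but it also describes performance as stable on most occasions, and practice common to both arms cancels in the interaction.

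**Conclusion.** The point holds as an avoidable loss of precision combined with an unspecified, data-dependent choice of analysis. It is not an invalid test. With equal SDs the default carries a variance 1/0.75 = 1.33 times that of ANCOVA at r = 0.5, or about 80% against 88% power at the planned 22 participants and the implied effect. The loss is larger at lower r and small at high r. Undeclared imbalance is over-corrected by (1−r) times its size, an error conditional on the imbalance that averages to zero over randomisation. Type I error is at risk only through discretion, up to about 0.07–0.08. These figures rest on equal SDs, an unstated r and the reading of 0.314 as Cohen's f. The unequal SDs of the cited group would make the variance ratio about 0.28–0.30 for r = 0.3–0.7, but they come from one pre–post group and serve only as a sensitivity check. The change is worth making because it uses data already collected.

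**What to change.** - State one primary analysis: ANCOVA of 12-week Alertness on group with baseline Alertness as covariate, or the equivalent baseline-adjusted model, whatever the baseline means look like.
- Use the same approach for the continuous secondary outcomes.
- Delete the rule that brings in ANCOVA only when baseline means are unmatched.
- Report the adjusted EXP − CON difference in original units with its 95% confidence interval.
- As a minor point, report within-arm changes over time descriptively, and say that they are not evidence of a group difference.

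The cost is a change of wording and one degree of freedom. No further participants, visits or measurements are needed.

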## Discussion

The presented study will be the first randomized controlled intervention trial combining physical and cognitive exercise in HD patients. By testing the possible beneficial effect of non-pharmacological interventions it will address a significant unmet need of dialysis patients. The foreseen achievements are to identify the benefits of combined physical exercise and cognitive training. We hypothesize that the experimental group will improve significantly and to a clinically meaningful effect size in cognitive and physical domains after the intervention compared to the control group. We will use novel instrumentation for sensitive detection of cognitive adaptation.

To the best of our knowledge, MMSE, MoCA, and Modified Mini-Mental State examination (3MS) are the most commonly used tests for cognitive screening in studies investigating the effects of different interventions on cognition in HD patients. Among the aforementioned instruments, MoCA has been shown to be the most suitable instrument for cognitive screening in the HD population with good sensitivity and specificity (Lee et al., 2018). However, the tests mentioned above are mostly used as screening tests for mild cognitive impairment and dementia and are not sensitive enough to detect intervention effects (Dong et al., 2010; Sheehan, 2012). Furthermore, all these tests are subject to learning effects, which limits the internal validity of prior studies. Accordingly, future studies should focus on selecting more specific and sensitive tests rather than using global/general cognitive tests and use the tests with low learning effect bias.

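### The fallback for non-normal outcomes (Friedman, then Sign-test) tests change over time only and contains no comparison of EXP with CON

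*Protocol article*

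**What the plan says.** All of the relevant text is in the protocol article, under Statistical Methods Including Sample Size Calculation, except the hypothesis, which is in the Discussion.

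- **Main analysis:** a mixed general linear model, "taking into account the groups (EXP and CON) and time (baseline and after 12 weeks) as factors".
- **Follow-up step:** "After determining the interaction effect, a secondary analysis will be used to determine the time effect in both groups".
- **Baseline imbalance:** "in the case of unmatched baseline means, the analysis of covariance (ANCOVA) with baseline measurements entered as a covariate will be applied".
- **Distribution check:** "Normality will be confirmed by using the Shapiro–Wilk test, with additional Q–Q plot visual inspection".
- **Fallback:** "For non-parametric data, a Friedman ANOVA will be applied, followed by a Sign-test separately for each scale".
- **The only two-sample rank test named:** "Mann–Whitney tests will be used to determine group differences in clinical and demographic variables".
- **Hypothesis (Discussion):** EXP is expected to improve "after the intervention compared to the control group".

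**The concern.** The trial randomises independent patients 1:1 to EXP or CON, so the evidence for an effect lies in the contrast between the arms. The linear model supplies that contrast through its group-by-time interaction. The fallback does not: it replaces a between-arm test with tests of whether patients changed.

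A significant change over time can come from the training, but also from practice on the test, regression to the mean or a general drift. The control arm is there to remove these, and it can do so only if the test uses it. The Discussion criticises earlier studies for learning effects, and the primary endpoint section cites training effects of low to moderate size for the TAP subtests. If this branch is used, a Friedman or Sign-test result is the only inferential result the article provides for that outcome, and it could easily be read as an intervention effect.

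**Working it through.** **1. What each test contains**

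| Method named in the article | Use stated | Compares EXP with CON? |
|---|---|---|
| Mixed linear model, group and time | Main effects on outcomes | Yes, through the interaction |
| ANCOVA on baseline | Outcomes, if baseline means differ | Yes |
| t test, chi-squared, Mann–Whitney | Clinical and demographic variables | Yes, but not stated for outcomes |
| Friedman | Non-parametric data | No: ranks repeated values within each patient |
| Sign-test | After Friedman, per scale | No: counts the signs of paired changes |

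Friedman cannot be turned into a test of the arms, because EXP and CON patients are independent and not matched blocks. Running it, or the Sign-test, in each arm separately gives two within-arm p-values and no comparison.

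**2. The sample size rests on a design the fallback does not analyse**

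Inputs from the article: effect size 0.314, alpha 0.05, power 0.80, N = 22. Assumed: the effect size is Cohen's f, two groups, two measurements, correlation 0.5.

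Noncentrality = f² × N × m / (1 − ρ) = 0.314² × 22 × 2 / 0.5 = 8.68, with 1 and 20 degrees of freedom. Power = 0.800, so the stated 22 is reproduced, at 11 per arm. The interaction test and the time test give the same N here, so the figure alone does not show which was intended.

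**3. Behaviour when both arms improve equally (no treatment effect)**

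Assumptions: 11 per arm; change normally distributed with SD 1; the same mean shift in both arms; Friedman on all 22 patients at baseline and 12 weeks. Each patient improves with probability p = Φ(shift).

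- Friedman with two visits: χ² = (plus − minus)² / n. With n = 22, a split of 16 to 6 gives 100/22 = 4.55, above 3.84; 15 to 7 gives 64/22 = 2.91, below it. The test therefore rejects when the number improving is at least 16 or at most 6.
- Exact Sign-test with n = 11: a split of 10 to 1 has two-sided p = 2 × 12/2048 = 0.012; 9 to 2 has p = 0.065. It rejects at 10 or more, or at 1 or fewer.
- EXP significant and CON not: s × (1 − s), where s is the rejection rate of one arm's Sign-test.

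| Shared shift (SD of change) | p | Friedman, pooled | Sign-test, one arm | EXP significant, CON not |
|---|---|---|---|---|
| 0 | 0.500 | 5% | 1% | 1% |
| 0.2 | 0.579 | 12% | 2% | 2% |
| 0.3 | 0.618 | 20% | 4% | 4% |
| 0.5 | 0.691 | 46% | 10% | 9% |
| 0.8 | 0.788 | 83% | 29% | 21% |

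These are exact binomial results. Simulation (4,000 trials per shift) gives 5, 11, 21, 46 and 84% for Friedman. In the same runs a between-arm Mann–Whitney test on the change rejects in 4 to 5% throughout.

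**4. Behaviour when the arms truly differ**

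If EXP improves by 0.5 SD and CON worsens by 0.5 SD, the true difference is 1 SD. Pooled Friedman rejects in about 3.5% of trials (exact), because the changes cancel. Mann–Whitney on the change rejects in 58% (simulation, 3,000 trials).

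**5. How likely is the branch?**

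The article quotes Alertness scores from an earlier study: SD/mean = 151.67/376.91 = 0.40 before treatment and 83.09/302.64 = 0.27 after. These ratios do not establish skewness. If scores were lognormal with those ratios (an assumption), Shapiro–Wilk at 0.05 would reject in about 24% of samples of 14 and 50% of samples of 28 at 0.40, and in about 15% and 28% at 0.27 (6,000 simulated samples each). The Edmonton Frail Scale, with a maximum of 17, and MoCA are bounded scores that could also take this route.

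**The case against.** - **Scope.** The sentence speaks of scales, which fits ordinal instruments such as the Edmonton Frail Scale at least as well as a reaction time, and the article never says outright that a Shapiro–Wilk failure on Alertness leads to Friedman. This stands as a limit on reach: the primary outcome is affected only if it is sent down this branch.
- **A third visit.** Outcomes are also measured 6 months after the intervention. Friedman followed by a Sign-test is a natural sequence for three visits, so the sentence may be meant as the rank version of the secondary within-group time analysis. That is possible, but the between-arm rank test is then simply absent, and the reader is still left with Friedman and Sign as the only stated option.
- **Mann–Whitney is named.** It is, but for clinical and demographic variables, in a sentence separate from the outcome analysis. Stretching the word clinical to cover outcomes would give outcomes two conflicting rules.
- **The rates are illustrative.** No document supports shifts of 0.5 or 0.8 SD. The article also says that performance on most TAP tasks was stable on repetition and gives this as a reason for choosing the test. At 0.2 SD the Friedman rate is only about 12%. The calculation uses normal changes and pools the arms, which the article does not specify. The high rates are power to detect a real time change and become errors only if read as a treatment effect. All of this stands.

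These points bear on how often, and how badly, the branch would mislead. None of them puts a group comparison into it.

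**Conclusion.** The concern holds. As written, the rule for non-parametric data contains no test of EXP against CON, so the hypothesis in the Discussion goes untested for every outcome that takes that route. This follows from the structure of the two tests and does not depend on the simulation.

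The size is conditional. With 11 per arm, normal changes and an equal improvement in both arms, a pooled Friedman test is significant in 12% of trials at a shared shift of 0.2 SD, 46% at 0.5 SD and 83% at 0.8 SD, against about 5% for a between-arm rank test. It can also miss a real difference between arms when their changes oppose each other. The defect is confined to the fallback: when the linear model or ANCOVA is used, the arms are compared. It must still be corrected, because the data decide whether the branch is used and the primary outcome could fall into it.

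**What to change.** Replace the fallback sentence with a between-arm rule, for example:

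- For skewed reaction times such as Alertness, log-transform and run the same baseline-adjusted comparison of EXP with CON.
- For ordinal scores, or where residuals remain clearly non-normal, use rank ANCOVA (Quade) or a Mann–Whitney test of EXP against CON on the 12-week change, reported with a Hodges–Lehmann difference and its 95% CI. Name one of the two in advance.
- Judge normality on model residuals, not on the raw scores.
- Drop Friedman and the Sign-test as tests of effect. If kept, label them as descriptive within-arm summaries of change over the visits.

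The cost is a sentence or two in the protocol or SAP. No additional patients, visits or measurements are needed.

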## Discussion

The presented study will be the first randomized controlled intervention trial combining physical and cognitive exercise in HD patients. By testing the possible beneficial effect of non-pharmacological interventions it will address a significant unmet need of dialysis patients. The foreseen achievements are to identify the benefits of combined physical exercise and cognitive training. We hypothesize that the experimental group will improve significantly and to a clinically meaningful effect size in cognitive and physical domains after the intervention compared to the control group. We will use novel instrumentation for sensitive detection of cognitive adaptation.

To the best of our knowledge, MMSE, MoCA, and Modified Mini-Mental State examination (3MS) are the most commonly used tests for cognitive screening in studies investigating the effects of different interventions on cognition in HD patients. Among the aforementioned instruments, MoCA has been shown to be the most suitable instrument for cognitive screening in the HD population with good sensitivity and specificity (Lee et al., 2018). However, the tests mentioned above are mostly used as screening tests for mild cognitive impairment and dementia and are not sensitive enough to detect intervention effects (Dong et al., 2010; Sheehan, 2012). Furthermore, all these tests are subject to learning effects, which limits the internal validity of prior studies. Accordingly, future studies should focus on selecting more specific and sensitive tests rather than using global/general cognitive tests and use the tests with low learning effect bias.

Combined cognitive and physical exercise training over a 3-month period improved executive function in older adults and was more effective than cognitive training or exercise training alone (Fabre et al., 2002; Anderson-Hanley et al., 2012). Moreover, in the pilot study (McAdams-Demarco et al., 2018b), cognitive training and exercise training performed separately were able to prevent decline in executive functions and psychomotor speed in HD patients. The results from a these limited studies in HD patients may support the hypothesis of a positive effect of cognitive and exercise training on cognitive function; however, a much better and clearer study design, especially to prevent the bias from learning effects and to secure adequate statistical power, is needed. Suppose there truly is a positive effect of physical exercise and/or cognitive training on cognitive function in dialysis patients, it is plausible that the strongest effects may be found with a combination of both interventions.

With this in mind, it is a reasonable step to combine the use of physical exercise and cognitive training with the aim of improving the functional (cognitive and physical) status of HD patients. HD procedure is a unique opportunity for the implementation of these types of combined interventions. In our research protocol, we address the unanswered questions by implementing the combined intervention and using more sensitive low learning effect cognitive tests. This research will also demonstrate the feasibility of using the innovative cognitive platform to apply cognitive training to HD patients. Ultimately, the basic knowledge gained can be used to develop appropriate interventions to mitigate the cognitive decline and maladaptation caused by physical inactivity. Based on our findings, we could develop guidelines and exercise protocols (physical and cognitive) aimed at improving cognitive and physical performance, thus improving the quality of life of HD patients. Importantly, in case our hypotheses will be confirmed, we will be able to offer evidence-based improvement of chronic renal replacement therapy programs.

